**Outcome measures**

Primary outcomes

The primary outcome measure is the change in weight (in kg) at 12 months post-randomisation.

Secondary outcomes

- Change in weight (in kg) at 1, 2, and 6 months post-randomisation.
- Change in BMI at 1, 2, 6 and 12 months post-randomisation. BMI is calculated as weight (in kg) divided by the square of height (in metres). The height measured at screening will be used for each follow-up assessment.
- Change in waist circumference (in cm) at 2, 6 and 12 months post-randomisation.
- Change in systolic blood pressure (mmHg) at 2, 6 and 12 months post-randomisation.
- Change in diastolic blood pressure (mmHg) at 2, 6 and 12 months post-randomisation.
- Change in the Food Craving Inventory score (Frequency domain) at 1, 2, 6, and 12 months post-randomisation.
- Change in the Food Craving Inventory score (Strength domain) at 1, 2, 6, and 12 months post-randomisation.
- Change in Food Knowledge Assessment Questionnaire score at 2, 6, and 12 months post-randomisation.
- Change in the Three Factor Eating Questionnaire score (Cognitive Restraint domain) at 2, 6, and 12 months post-randomisation.
- Change in the Three Factor Eating Questionnaire score (Uncontrolled Eating domain) at 2, 6, and 12 months post-randomisation.
- Change in the Three Factor Eating Questionnaire score (Emotional Eating domain) at 2, 6, and 12 months post-randomisation.
- Change in the International Physical Activity Questionnaire (IPAQ) score (MET-minutes/week domain) at 2, 6, and 12 months post-randomisation.
- Change in the International Physical Activity Questionnaire (IPAQ) score (Sitting domain) at 2, 6, and 12 months post-randomisation.
- Proportion of participants losing 5% of body weight at 2, 6, and 12 months post-randomisation.
- Proportion of participants losing 10% of body weight at 2, 6, and 12 months post-randomisation.

Scoring details for the Food Craving Inventory, the Food Knowledge Assessment Questionnaire, the Three Factor Eating Questionnaire, and the International Physical Activity Questionnaire are available in Appendix 2.

Weight, BMI, waist and blood pressure outcomes were measured by researchers who were blind to treatment arm. These researchers were affiliated with the trial team, but were involved only in collecting outcomes during follow-up, and had no role in providing the intervention, and no contact with patients other than whilst collecting follow-up measurements.

1. **STUDY METHODS**

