**Baseline**

The following variables were collected at baseline

- ***Demographics:*** includes age, sex, ethnicity, employment, level of education
- ***Health and lifestyle:*** includes smoking status, alcohol consumption, and general health
- ***Weight loss history:*** includes number of past weight-loss attempts, methods used, most weight ever lost, and regular monitoring of weight.
- ***Concurrent medications:*** all current medications are recorded.
- ***Height and weight:*** measured in centimeters and kilograms. BMI calculated from these.
- ***Waist circumference:*** measured in centimetres.
- ***Blood pressure:*** resting blood pressure recorded.

The following validated questionnaires are also administered at baseline:

- International Physical Activity Questionnaire [4]
- Food knowledge assessment
- Food craving inventory [5]
- Three Factor Eating Questionnaire [6]
- EQ-5D
- Use of health services questionnaire

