**General analysis principles**

The main analysis for each outcome will use intention-to-treat (ITT) principles, meaning that all participants with a recorded outcome will be included in the analysis, and will be analysed according to the treatment group to which they were randomised. More information on which participants will be included in each analysis is available in the section below. All p-values will be two sided, and the significance level is set at 5%.

Analyses for all outcomes will be presented as:

- The number of participants included in the analysis, by treatment group;
- A summary measure of the outcome, by treatment group (e.g. mean (SD) for continuous outcomes, number (%) for binary outcomes);
- A treatment effect, with a 95% confidence interval;
- A two-sided p-value.

All analyses will account for clustering by group in the intervention arm, and clustering by nurse in the control arm. Each patient will be defined as belonging to a cluster, defined by which group they belonged to if they were in the intervention arm, and which nurse they were treated by if they were in the control arm. This variable will be included as a random intercept in a mixed-effects regression model. This analysis assumes the intraclass correlation coefficient is the same between groups in the intervention arm as it is between nurses in the control arm. The Kenward-Roger degree-of-freedom correction will be employed for all linear mixed-effects models.

All analyses will adjust for baseline weight, age, gender, ethnicity (White British, White other, Black, Asian, Mixed, or other), smoking status (smoker vs. non-smoker) and GP practice (Lawson vs. Barkantine) as covariates in a regression model. Outcomes which are measured at baseline will also be adjusted for the value of the outcome at baseline (this includes weight, BMI, waist circumference, systolic and diastolic blood pressure, Food Craving Inventory, Food Knowledge Assessment, Three Factor Eating Questionnaire, and IPAQ). Continuous covariates (baseline weight, age) will be assumed to have a linear association with outcome. Binary and categorical covariates (gender, ethnicity, smoking status, and GP practice) will be included in the regression model using indicator (dummy) variables. Missing baseline data will be accounted for using mean imputation.

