**Analysis of secondary outcomes**

*Change in weight at 1, 2, and 6 months*

This outcome will be included in the same model as the primary outcome.

*Change in BMI at 1, 2, 6 and 12 months*

These outcomes will be analysed using the same method as change in weight at 6 and 12 months, with the exception that baseline BMI will be included as a covariate in the regression model, as opposed to baseline weight. BMI measurements at 1, 2, 6, and 12 months will be included in the model.

*Change in waist circumference at 2, 6 and 12 months*

These outcomes will be analysed using the same method as change in weight at 6 and 12 months with the exception that baseline waist circumference will be included as a covariate in the regression model, as opposed to baseline weight. Waist circumference measurements at 2, 6, and 12 months will be included in the model.

*Change in systolic blood pressure at 2, 6 and 12 months*

These outcomes will be analysed using the same method as change in weight at 6 and 12 months. The baseline value of systolic blood pressure will also be included as a covariate in the model. Systolic blood pressure measurements at 2, 6, and 12 months will be included in the model.

*Change in diastolic blood pressure at 2, 6 and 12 months*

These outcomes will be analysed using the same method as change in weight at 6 and 12 months. The baseline value of diastolic blood pressure will also be included as a covariate in the model. Diastolic blood pressure measurements at 2, 6, and 12 months will be included in the model.

*Change in Food Craving Inventory (frequency domain) at 1, 2, 6 and 12 months*

These outcomes will be analysed using the same method as change in weight at 6 and 12 months. The baseline value of the Food Craving Inventory (frequency domain) will also be included as a covariate in the model. Frequency domain measurements at 2, 6, and 12 months will be included in the model.

Treatment effect estimates will only be presented at 6 and 12 months; data from month 2 is included in the model to increase power, and to make the missing-at-random assumption more plausible.

*Change in Food Craving Inventory (strength domain) at 1, 2, 6 and 12 months*

These outcomes will be analysed using the same method as change in weight at 6 and 12 months. The baseline value of the Food Craving Inventory (frequency domain) will also be included as a covariate in the model. Strength domain measurements at 2, 6, and 12 months will be included in the model.

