*Change in Food Knowledge Assessment at 2, 6 and 12 months*

These outcomes will be analysed using the same method as change in weight at 6 and 12 months. The baseline value of food knowledge will also be as a covariate in the model. Food Knowledge Assessment measurements at 2, 6, and 12 months will be included in the model.

*Change in Three Factor Eating Questionnaire (Cognitive Restraint domain) at 2, 6 and 12 months*

These outcomes will be analysed using the same method as change in weight at 6 and 12 months. The baseline value of the Three Factor Eating Questionnaire (Cognitive Restraint domain) will also be included as a covariate in the model. Cognitive Restraint domain measurements at 2, 6, and 12 months will be included in the model.

*Change in Three Factor Eating Questionnaire (Uncontrolled Eating domain) at 2, 6 and 12 months*

These outcomes will be analysed using the same method as change in weight at 6 and 12 months. The baseline value of the Three Factor Eating Questionnaire (Uncontrolled Eating domain) will also be included as a covariate in the model. Uncontrolled Eating domain measurements at 2, 6, and 12 months will be included in the model.

*Change in Three Factor Eating Questionnaire (Emotional Eating domain) at 2, 6 and 12 months*

These outcomes will be analysed using the same method as change in weight at 6 and 12 months. The baseline value of the Three Factor Eating Questionnaire (Emotional Eating domain) will also be included as a covariate in the model. Emotional Eating domain measurements at 2, 6, and 12 months will be included in the model.

*Change in International Physical Activity Questionnaire (MET-minutes/week domain) at 2, 6 and 12 months*

These outcomes will be analysed using the same method as change in weight at 6 and 12 months. The baseline value of the MET-minutes/week domain will also be included as a covariate in the model. MET-minutes/week domain measurements at 2, 6, and 12 months will be included in the model.

*Change in International Physical Activity Questionnaire (sitting domain) at 2, 6 and 12 months*

These outcomes will be analysed using the same method as change in weight at 6 and 12 months. The baseline value of the sitting domain will also be included as a covariate in the model. Sitting domain measurements at 2, 6, and 12 months will be included in the model.

*Proportion of participants losing 5% of body weight at 2, 6, and 12 months*

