**Food Craving Inventory score**

Each of the five food types (fatty foods, carbohydrates and starches, sweet foods, savoury snacks, and fruit) is assigned a score from 0 to 5 on both frequency and urge of craving. The frequency domain is then calculated by summing the scores of the individual questions related to frequency; the strength domain is calculated in a similar manner. The overall scores from both domains range from 0 to 25, with higher scores indicating more frequent or stronger urges.

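### The Food Craving Inventory strength analysis names the frequency-domain baseline as its covariate, against the plan's own-baseline rule, so the model for this secondary outcome is not fixed

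*SAP*

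**What the plan says.** The SAP treats strength of craving as a secondary outcome separate from frequency. Under Outcome measures it lists "Change in the Food Craving Inventory score (Strength domain) at 1, 2, 6, and 12 months post-randomisation". Appendix 2 gives each domain its own total from 0 to 25; after describing the frequency score it adds that "the strength domain is calculated in a similar manner". The inventory is among the questionnaires given at baseline, and Table 1 has a row for baseline strength. A baseline strength value is therefore planned for.

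General analysis principles sets the adjustment rule: "Outcomes which are measured at baseline will also be adjusted for the value of the outcome at baseline". The list that follows names the Food Craving Inventory but does not separate its two domains.

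In Analysis of secondary outcomes, the strength paragraph says "The baseline value of the Food Craving Inventory (frequency domain) will also be included as a covariate in the model. Strength domain measurements" at the later visits. The covariate sentence is identical to the one in the frequency paragraph directly above it, where it fits, since there "Frequency domain measurements at 2, 6, and 12 months will be included in the model".

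**The concern.** The strength paragraph is the only text that says which domain's baseline enters this model, and it names the other domain. The general rule points to baseline strength. The two texts leave three possible models: frequency baseline only, strength baseline only, or both. A pre-specified plan should leave one.

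The choice matters because the outcome is a change score. A change score is negatively related to its own baseline whenever the baseline-to-follow-up correlation is below 1. Adjusting for the outcome's own baseline removes that part of the variance and corrects for chance imbalance between the arms. Adjusting for a different, correlated score does both jobs only in part.

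**Working it through.** **1. Comparison of the paragraphs.** Twelve continuous secondary outcomes have their own paragraph in Analysis of secondary outcomes.

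| Outcome | Baseline named |
|---|---|
| BMI; waist circumference | own, in place of baseline weight |
| Systolic; diastolic blood pressure | own |
| Food Craving Inventory, frequency | own |
| **Food Craving Inventory, strength** | **frequency** |
| Food Knowledge Assessment | own |
| Three Factor Eating Questionnaire, three domains | own domain |
| IPAQ, two domains | own domain |

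Eleven of the twelve name their own baseline. The nearest comparison is another questionnaire with several domains, for example "The baseline value of the Three Factor Eating Questionnaire (Uncontrolled Eating domain) will also be included as a covariate in the model" for Uncontrolled Eating. Weight at the earlier visits sits in the primary model, which adjusts for baseline weight. The 5% and 10% weight-loss outcomes are binary and have no separate baseline score, so they are outside the comparison.

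**2. Size if baseline strength is omitted.** The SAP gives no figure that depends on this point and none of the correlations needed, so what follows is an illustration.

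Assumptions:
- one follow-up time, independent patients, unit variances;
- ρ is the correlation of baseline with follow-up strength, taken as 0.3 to 0.7;
- r is the correlation of strength with frequency at baseline, taken as 0.4 to 0.8;
- the correlation of baseline frequency with follow-up strength is the product r·ρ.

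Residual variance of the change score:
- adjusted for own baseline: 1 − ρ²;
- adjusted for baseline frequency only: the change has variance 2(1 − ρ) and covariance −r(1 − ρ) with baseline frequency, which leaves 2(1 − ρ) − r²(1 − ρ)².

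| ρ | r | Own baseline | Frequency only | Variance ratio | SE ratio |
|---|---|---|---|---|---|
| 0.3 | 0.4 | 0.910 | 1.400 − 0.0784 = 1.322 | 1.452 | 1.205 |
| 0.3 | 0.8 | 0.910 | 1.400 − 0.3136 = 1.086 | 1.194 | 1.093 |
| 0.5 | 0.6 | 0.750 | 1.000 − 0.0900 = 0.910 | 1.213 | 1.10 |
| 0.7 | 0.4 | 0.510 | 0.600 − 0.0144 = 0.586 | 1.148 | 1.072 |
| 0.7 | 0.8 | 0.510 | 0.600 − 0.0576 = 0.542 | 1.064 | 1.031 |

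The standard error is about 3% to 21% larger, and about 10% larger at the middle values.

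**3. Chance imbalance.** Suppose the arms differ by d in baseline strength, and baseline frequency differs by its expected r·d. With frequency-only adjustment, a share (1 − ρ)(1 − r²) of d stays in the estimated effect, with reversed sign. At ρ = 0.5 and r = 0.6 this is 0.5 × 0.64 = 0.32. With own-baseline adjustment the share is zero.

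**4. If both baselines are included.** Under the product assumption, baseline frequency carries no further information on follow-up strength once baseline strength is in the model. The residual variance is then 1 − ρ² again, and the cost is one redundant covariate.

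**The case against.** The strongest reply is that nothing is left out. The strength paragraph uses the same method as the weight outcome. That method takes in the covariates of section 5, where the own-baseline rule stands and the Food Craving Inventory is listed. The strength paragraph says that frequency is *also* included, which is additive wording. Where the SAP wants one baseline to replace another, as for BMI and waist circumference, it says so. Read together, the texts give a model with baseline strength plus a redundant baseline frequency, and the losses above do not arise.

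This reading is available, and it rules out the stronger claim a reader might infer: that the plan definitely leaves the outcome's own baseline out of its model. It does not settle the matter. In most of the neighbouring paragraphs the same *also* sentence is how the outcome's own baseline is named, so an analyst could equally take it as the full instruction and enter frequency in place of strength.

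A reader might also infer that regression to the mean would bias the comparison. The documents do not support that. Participants were individually randomised, so regression to the mean is expected to be equal in both arms and to cancel. Only chance imbalance in the realised sample matters.

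The precision figures have limits too. The planned model has repeated measures and a random intercept for cluster, and a patient-level covariate need not reduce variance between clusters. The percentages therefore do not transfer directly to that model. The sample size is based on weight, so no stated power figure changes.

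**Conclusion.** The strength paragraph is wrong as written. It names the baseline of another domain, conflicts with the SAP's general rule, and differs from every other continuous secondary outcome. The identical sentence just above makes a copying error the likely cause, and the SAP gives no reason for adjusting across domains.

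The consequence is an ambiguous model for one secondary outcome; omission of baseline strength is possible but not certain. The 3% to 21% range, and the imbalance left uncorrected, apply only if baseline strength is omitted, and they rest on the assumed correlations and the simplified model. The treatment effect stays unbiased in expectation, and the primary analysis is untouched. This is a small but clear correction.

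**What to change.** In the strength-domain paragraph of Analysis of secondary outcomes, replace frequency domain with strength domain in the covariate sentence. This restores agreement with General analysis principles and leaves one model. In General analysis principles, the entry for the Food Craving Inventory could also say that each domain is adjusted for its own baseline. The cost is one word in the SAP and one variable in the analysis code, with no change to design or data collection.

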**Sample size determination**

A clinically significant effect can be achieved with 3-5 kg weight loss in obese people.[3] We assumed that WAP would increase weight loss by 2.6kg compared with usual care (WAP 3kg vs. usual care 0.4kg) for participants available for follow-up at one year, and that there would be no difference in weight loss between treatment groups for participants not available for follow-up. Assuming that 50% of participants in both treatment groups were available for follow-up at one year, the difference in weight loss between groups would be 1.3kg (WAP 1.5kg vs. usual care 0.2kg). Assuming a standard deviation of 3 in both treatment groups, and a 5% two-sided significance level, we would require 112 participants in each group to detect this mean difference with 90% power. Our estimate of 50% loss to follow-up is conservative and based on international experience in this field and existing data from similar underprivileged and highly mobile populations and interventions.

To account for potential clustering effects due to group treatment in the intervention arm, assuming a mean cluster size of 18 and an intra-cluster correlation coefficient of 0.05, a total of 208 individuals will be required in the intervention arm. The same power can be achieved with 108 in the control arm and 216 in the intervention arm which we have increased to 110 in the control arm and 220 in the intervention arm to give an allocation ratio between the two arms (2:1) which can be expressed in whole numbers. Thus we require a total of 330 individuals for the entire study

1. **DATA COLLECTION**

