These outcomes will be analysed using a mixed-effects logistic regression model. The model will include whether the participant had lost 5% of their body weight at 2, 6 and 12 months as outcomes.

The model will include three levels: the top level will include a random intercept for ‘cluster’ (group or nurse, depending on treatment arm). The second level will include a random intercept for patient, and a random slope for time point. Treatment arm, time point, and the interaction between treatment arm and time point will be included in the model as fixed factors. Time point will be included as an indicator variable. The covariates listed in section 5 will also be included in the model as fixed factors.

The analysis will be implemented in Stata as follows:

meqrlogit outcome treatment##time covariates || cluster_id:, || ///

patient_id: time, cov(exch)

If this model fails to converge, we will run the model again after removing the random slope for time at the second level.

*Proportion of participants losing 10% of body weight at 2, 6, and 12 months*

These outcomes will be analysed using the same methods as the proportion of participants losing 5% of body weight at 2, 6, and 12 months.

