**Table 4 – Results for primary and secondary outcomes**

|  | **Usual care (n=…)** | **WAP (n=…)** | **Treatment effect* (95% CI)** | **P-value** |
| --- | --- | --- | --- | --- |
| Change in weight (kg) – mean (SD) |  |  |  |  |
| 1 month |  |  |  |  |
| 2 months |  |  |  |  |
| 6 months |  |  |  |  |
| 12 months |  |  |  |  |
| Change in BMI – mean (SD) |  |  |  |  |
| 1 month |  |  |  |  |
| 2 months |  |  |  |  |
| 6 months |  |  |  |  |
| 12 months |  |  |  |  |
| Change in waist circumference (cm) – mean (SD) |  |  |  |  |
| 2 months |  |  |  |  |
| 6 months |  |  |  |  |
| 12 months |  |  |  |  |
| Change in systolic blood pressure – mean (SD) |  |  |  |  |
| 2 months |  |  |  |  |
| 6 months |  |  |  |  |
| 12 months |  |  |  |  |
| Change in diastolic blood pressure – mean (SD) |  |  |  |  |
| 2 months |  |  |  |  |
| 6 months |  |  |  |  |
| 12 months |  |  |  |  |
| Change in Food Craving Inventory score (Frequency domain) – mean (SD) |  |  |  |  |
| 1 month |  |  |  |  |
| 2 months |  |  |  |  |
| 6 months |  |  |  |  |
| 12 months |  |  |  |  |
| Change in Food Craving Inventory score (Strength domain) – mean (SD) |  |  |  |  |
| 1 month |  |  |  |  |
| 2 months |  |  |  |  |
| 6 months |  |  |  |  |
| 12 months |  |  |  |  |
| Change in Food Knowledge Assessment Questionnaire score – mean (SD) |  |  |  |  |
| 2 months |  |  |  |  |
| 6 months |  |  |  |  |
| 12 months |  |  |  |  |
| Change in Three Factor Eating Questionnaire score (Cognitive Restraint domain) – mean (SD) |  |  |  |  |
| 2 months |  |  |  |  |
| 6 months |  |  |  |  |
| 12 months |  |  |  |  |
| Change in Three Factor Eating Questionnaire score (Uncontrolled Eating domain) – mean (SD) |  |  |  |  |
| 2 months |  |  |  |  |
| 6 months |  |  |  |  |
| 12 months |  |  |  |  |
| Change in Three Factor Eating Questionnaire score (Emotional Eating domain) – mean (SD) |  |  |  |  |
| 2 months |  |  |  |  |
| 6 months |  |  |  |  |
| 12 months |  |  |  |  |
| Change in International Physical Activity Questionnaire (MET-minutes/week domain) – mean (SD) |  |  |  |  |
| 2 months |  |  |  |  |
| 6 months |  |  |  |  |
| 12 months |  |  |  |  |
| Change in International Physical Activity Questionnaire (Sitting domain) – mean (SD) |  |  |  |  |
| 2 months |  |  |  |  |
| 6 months |  |  |  |  |
| 12 months |  |  |  |  |
| Participants losing 5% of their body weight – no. (%) |  |  |  |  |
| 2 months |  |  |  |  |
| 6 months |  |  |  |  |
| 12 months |  |  |  |  |

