| Participants losing 10% of their body weight – no. (%) |  |  |  |  |
| 2 months |  |  |  |  |
| 6 months |  |  |  |  |
| 12 months |  |  |  |  |

*Treatment effects are presented as a difference in means (estimated from a mixed-effects regression model) between the two groups (WAP vs. control) for all outcomes apart for the number of participants who lost 5% or 10% of their body weight, where the treatment effect is presented as an odds ratio.

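### The 5% and 10% weight-loss odds ratios are conditional on patient and cluster effects, but Table 4 prints them unlabelled beside raw percentages, from which they will differ whenever there is an effect

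*SAP*

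**What the plan says.** The Outcome measures section defines these two secondary outcomes as proportions of participants at 2, 6 and 12 months. Under Analysis of secondary outcomes they are analysed by mixed-effects logistic regression in which "the top level will include a random intercept for ‘cluster’ (group or nurse, depending on treatment arm"). At the next level, "The second level will include a random intercept for patient, and a random slope for time point". The Stata line codes this level as "patient_id: time, cov(exch"). The fallback is: "If this model fails to converge, we will run the model again after removing the random slope for time at the second level". The patient intercept therefore stays in either case.

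For reporting, General analysis principles asks for "number (%) for binary outcomes" by arm, and the Table 4 row is headed "Participants losing 5% of their body weight – no" (with the percentage). The Table 4 footnote says that these are the rows "where the treatment effect is presented as an odds ratio". Nowhere does the SAP say what kind of odds ratio this is, and it plans no risk difference or population-averaged odds ratio.

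**The concern.** In a logistic model with a patient random intercept, the treatment coefficient contrasts two patients with the same random effect. The percentages in the same row describe whole arms. On the odds-ratio scale these are different quantities, and the conditional one is further from 1. In the linear-model rows of Table 4 the same layout does no harm, because a random effect does not change the meaning of a mean difference.

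Weight change is likely to be correlated within a patient across visits, so the patient variance on the logit scale may be large. A reader of the row will naturally take the odds ratio as the contrast of the two percentages beside it. Its size will in fact depend partly on how consistent patients are from visit to visit, not only on how many more of them reached the threshold. Six cells are affected: two outcomes at three visits.

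**Working it through.** **The plan's own figure.** The SAP gives no odds ratio, arm-specific responder rate, patient variance or between-visit correlation for these outcomes. The figure that can be checked is the sample size: 2 × (1.960 + 1.282)² × 3² / 1.3² = 111.9, so 112 per arm, as stated in Sample size determination. This confirms that the planning SD of 3 kg goes with the 1.3 kg difference.

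**Inputs from Sample size determination.** Mean losses of 1.5 v 0.2 kg (all randomised) and "WAP 3kg vs. usual care 0.4kg" (those followed up); SD 3 kg. Using SD 3 for the second pair is an extension of the plan.

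**Assumed inputs.** Body weight of 95 kg, so 5% is 4.75 kg; the same means at each visit; normally distributed weight change; equal correlation ρ between visits of 0.5, 0.65 or 0.8.

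**Step 1: odds ratio implied by the percentages.** p = 1 − Φ((4.75 − mean)/3).
- 3 v 0.4 kg: z = 0.583 and 1.450, so p = 28.0% v 7.35%. Odds 0.3885/0.0793 = 4.90.
- 1.5 v 0.2 kg: z = 1.083 and 1.517, so p = 13.9% v 6.5%. Odds 0.1618/0.0692 = 2.34.

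**Step 2: odds ratio from a patient random-intercept logistic model.** This is a large-sample maximum likelihood fit to the three-visit response patterns, 2:1 allocation, without cluster effect or covariates.

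| Mean losses | ρ | Patient SD (logit) | Implied OR | Conditional OR | Factor |
|---|---|---|---|---|---|
| 1.5 v 0.2 kg | 0.5 | 1.79 | 2.34 | 3.10 | 1.3 |
| 1.5 v 0.2 kg | 0.65 | 2.44 | 2.34 | 3.80 | 1.6 |
| 1.5 v 0.2 kg | 0.8 | 3.56 | 2.34 | 5.73 | 2.5 |
| 3 v 0.4 kg | 0.5 | 1.73 | 4.90 | 8.87 | 1.8 |
| 3 v 0.4 kg | 0.65 | 2.38 | 4.90 | 13.5 | 2.8 |
| 3 v 0.4 kg | 0.8 | 3.51 | 4.90 | 31.2 | 6.4 |

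Moving the threshold between 4.5 and 5 kg (90 to 100 kg) changes the factors little: 6.2 to 6.5 in the last row, for example.

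**Step 3: hand check.** The usual approximation is log OR(conditional) ≈ log OR(marginal) × √(1 + 0.346σ²). For the first row, √(1 + 0.346 × 1.79²) = 1.45 and 2.34^1.45 ≈ 3.4, against 3.10 from the fit: same direction, similar size. With no effect the logarithm is 0 and the factor is exactly 1.

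**Step 4: the random slope.** The first-choice model adds a slope on `time`, entered without a factor prefix and with exchangeable covariance, so intercept and slope share one variance. With a correlation of 0.6 between adjacent visits (0.6^1.5 between 2 and 12 months) and 3 v 0.4 kg, the implied odds ratio is 4.90 at every visit. The fitted conditional odds ratios at 2, 6 and 12 months are:
- time coded 2/6/12: 5.8, 10.9 and 40.3 (factors 1.2, 2.2 and 8.2);
- time coded 1/2/3: 7.2, 10.7 and 17.2 (factors 1.5, 2.2 and 3.5).

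For 1.5 v 0.2 kg the 12-month factors are 2.9 and 1.8 to 1.9 respectively. The intercept–slope correlation was estimated at or close to 1 in these fits, so the sizes are indicative. They do show that the result depends on visit and on time coding, which the SAP does not state. The 10% outcome was not computed separately; the mechanism is the same.

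**The case against.** A conditional odds ratio is a legitimate estimand. The SAP openly specifies a mixed-effects logistic model, the null hypothesis is the same on both scales, and the test of no effect stays broadly valid. All of that stands. A reader might infer that the analysis is biased or its test unsound; the documents do not support that.

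Nor are the raw percentages a standard of correctness. Every analysis is covariate-adjusted, and the model uses patients with any follow-up under missing-at-random, whereas the percentages come from those observed. Even a population-averaged estimate would not match them exactly. That stands too, but it concerns a different discrepancy, and it does not make a patient-specific odds ratio a contrast of proportions.

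The percentages are printed in the same row, so the absolute difference remains visible, and these are secondary outcomes; the primary is weight change in kg. This limits the harm. It does not remove the mismatch, because nothing tells the reader that the odds ratio and the percentages answer different questions.

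A reader might also infer a fixed inflation, say 2 to 6 times. The documents cannot support that: the correlation that drives the factor is assumed, three of the six scenarios above fall below 2, and the slope model gives values both below and above such a range.

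**Conclusion.** The point holds as a flaw of reporting and interpretation in two secondary outcomes. As planned, the printed odds ratio will lie further from 1 than its own row implies whenever there is a treatment effect and patient-level variance. If WAP did worse, it would overstate the disadvantage in the same way.

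With a random-intercept model, SD 3 kg, a 4.75 kg threshold and correlations of 0.5 to 0.8, the factor is about 1.3 to 2.5 for 1.5 v 0.2 kg and 1.8 to 6.4 for 3 v 0.4 kg. It is 1 with no effect. Under the planned slope it varies by visit and time coding, and it can exceed that range at 12 months. Threshold, correlation and constant means over visits are assumptions; the SAP supplies only the means and the SD.

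**What to change.** Keep the model. In the text for the 5% and 10% outcomes and in the Table 4 footnote, add a population-averaged risk difference and odds ratio at 2, 6 and 12 months, each with a 95% CI. Obtain them by averaging the fitted model's predicted probabilities over the random effects and the observed covariates, with every participant set to each arm in turn. Label any odds ratio taken directly from the model as conditional (patient-specific). Whether that one stays in the main column is a matter of preference once it is labelled. State also how `time` is coded in the random slope and confirm that the exchangeable covariance is intended, since the conditional odds ratio depends on both.

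The cost is a few sentences of SAP text and some post-estimation code. The downside for the authors is a headline odds ratio closer to 1.
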